### Randomization

We will determine pairs of comparable wards (number of patients, distribution of diagnoses, staff etc.) and then randomize one ward of each pair to the intervention and one ward to the control condition (i.e. cluster-randomization). While the principal investigators will determine the paired wards, the randomization will be done by the statistical department of the medical faculty at our university, Institut für Medizinische Statistik und Epidemiologie (IMSE).

A cluster-randomized design in which the unit of randomization is the psychiatric ward is seen as necessary to prevent contamination of intervention and control conditions [19].

### Blinding

Due to the nature of the intervention (staff training, patient training) there will be no blinding. Likewise a blinding of raters is not applicable because most ratings, including the main outcome measure, are “subjective” self-ratings. However, the analysis will be performed by a statistician who will be blinded as to patient allocation.

To avoid selection bias all patients fulfilling inclusion criteria will be recruited consecutively in the intervention and control group. This process will be monitored by the study center and will be reported in form of a CONSORT diagram. The number of patients who do not consent will be carefully documented together with their underlying reason for refusal.

### Statistical analyses

To assess the effect of the intervention on the continuous primary outcome, a random effects linear regression model will be fitted with ward (cluster) as a random effect term and intervention group as a fixed effect. The point estimate for the intervention effect will be reported together with the corresponding 95% confidence interval. A *p*-value <0.05 will be considered as providing statistical significant evidence of a group difference. In addition, models adjusting for baseline covariates such as severity of illness, admission status and variables with a large baseline imbalance will be fitted in secondary analyses. An intention to treat approach will be taken to the analysis, i.e. patients in intervention clusters will be analyzed in this group (if outcome data are available) even if they don’t receive all of the planned intervention.

Exploratory analyses will be performed to assess the effect of the intervention on the secondary outcome measures. Furthermore, it will be assessed if SDM is a mediator for the secondary outcomes following the criteria of Baron and Kenny. Random effect linear models will be fitted to the continuous secondary outcome measures, analogous to the primary analysis. For binary secondary outcome measures, logistic regression models using GEEs will be fitted.

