#### Baseline parameters

For all patients enrolled socio-demographics, diagnosis, illness severity (CGI and GAF scores) and data on illness history (previous hospitalizations, duration of illness etc.) will be recorded at baseline (at study entry).

Since decision making and patients’ perception of decision making may be influenced by patients’ participation preferences, the Autonomy Preference Index (API [25]) will be obtained. The API is a four item questionnaire assessing patients’ general desire to participate in decision making. API scores have been shown to be associated with treatment satisfaction and health care outcomes [26]. Further, a recently developed questionnaire addressing patients’ competence for shared decision making (PatPart-19) will also be used. This 19 item questionnaire covers the subscales open communication, critical communication and adherence in therapy and was validated in two large samples of psychiatric inpatients (Kohl et al., in preparation). In addition, active patient decision making has been shown to be related to patients’ having less unmet needs [27]. Therefore, the Camberwell Assessment of Need self-report questionnaire (CANSAS-P), a 22-item questionnaire addressing patients’ needs for support in various domains will be applied. As SDM-PLUS focusses on critical decision processes in which disagreement between patients and physicians may occur we aim to identify patients with potentially reduced insight, allowing for subgroup analyses in patients with or without insight. We will administer the Birchwood Insight Scale [28], an eight-item questionnaire addressing insight, necessity of medication or treatment. Likewise patients’ perception of the current admission (i.e. the extent to which patients perceived the admission as involuntary) will be recorded using the MacArthur Admission Experience Survey as used by O’Donoghue et al. 2013 [29].

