#### Secondary outcomes

As outlined above, a better involvement of patients in medical decisions and health care professionals better addressing “difficult decisions” may also result in a better therapeutic relationship, higher treatment satisfaction, fewer unmet needs, more thoroughly implemented therapies, improved adherence, and probable reduced relapse rates (see Fig. 1). These outcomes will be obtained at T1 (three weeks after study enrolment) and during a one year follow up with quarterly assessments (T2-T5).

Patients’ involvement in medical decisions from the patients’ point of view will be obtained as the primary outcome measure at T1 and as a secondary outcome during follow up (T2-T5). In addition, physicians will provide their view on patients’ involvement using the physician version of the SDM-Q-9 at T2-T5 (SDM-Q-Doc [31]). As most patients will have changes in their treating psychiatrist when switching from inpatient to outpatient treatment, the SDM-Q-9 refers to the inpatient psychiatrist at T1 and to the outpatient psychiatrists at T2-T5.

Whether or not the intervention also has an influence on the therapeutic relationship will be determined using the Helping Alliance Scale at T2-T5, which has a patient (HAS-P) and a clinician (HAS-C) version [32]. The HAS comprises five items rated on a visual analogue scale ranging from 0 (‘not at all’) to 10 (‘extremely well’). While HAS-P includes items on ‘right treatment’, ‘understood by therapist’, ‘criticized by therapist’, ‘committed therapist’ and ‘trust therapist, HAS-C items cover ‘getting along with patient’, ‘understand patient’, ‘look forward to meeting patient’, ‘feel actively involved’, and ‘feel I can help patient’.

Treatment satisfaction will be measured using the Questionnaire on Patients’ Treatment Satisfaction (ZUF8) at T1, an eight-item questionnaire addressing general satisfaction with hospital care [33]. The prevalence of unmet needs on the patients’ side after intervention will be assessed using the Camberwell Assessment of Need self-report questionnaire (CANSAS-P) also at T1 and T2 [34]. For the assessment of adherence, patients will fill out the Medication Adherence Rating Scale at T2–T5 (MARS [35]). This measure also includes the 10 items of the Drug Attitude Inventory allowing for an analysis of patients’ drug attitudes.

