In addition, aspects of patients’ well-being and quality of life will be addressed using the WHO-5 well-being index and the EUROHIS-QOL index at T3 and T5. The WHO-5 index is a five item self-report measure of general well-being and the EUROHIS-QOL is an 8-item self-assessment instrument of generic quality of life. Both instruments were validated in German versions and yielded good to excellent psychometric properties [36].

Another aspect of interest is whether or not SDM-PLUS supports clinicians in addressing “difficult medical decisions”. This assumption is based on evidence that the discussion of certain decisions (e.g. long acting antipsychotic injectable) is often avoided by psychiatrists resulting in low implementation rates for these treatments [37]. To document the discussion and implementation of “difficult medical decisions” we will perform a semi-structured interview with the psychiatrists in charge at T1. This interview will – for every patient participating in the study - cover four domains: “difficult compounds”, “difficult other therapies such as ECT”, “difficult psychosocial interventions such as legal guardianship”, and “difficult other decisions as specified by the psychiatrist”. For each domain it will be documented whether or not there was any need for discussing decisions, whether there was a discussion and whether any decisions were implemented. Data gathered in this interview will result in two “sum scores” of difficult decisions (number of decisions addressed, number of decisions implemented).

In addition, we will obtain at discharge, the length of the inpatient stay, the future psychiatrist after discharge and a brief description of discharge medication (antipsychotics prescribed: yes/no, LAI prescribed: yes/no, monotherapy with antipsychotics vs polypharmacy with antipsychotics: yes/no). Outpatient psychiatrists will be asked to document any rehospitalization of their patients, their estimate of the patient’s adherence (one item visual analogue scale), CGI and GAF scores at T2–T5.

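### The primary model omits collected baseline covariates, secondary adjustment is partly chosen by observed imbalance, and CANSAS-P, CGI and GAF are modelled with no stated own-baseline term

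*Protocol article*

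**What the plan says.** All references are to the protocol article.

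- **Primary model.** Under Statistical analyses, the random effects linear regression is "fitted with ward (cluster) as a random effect term and intervention group as a fixed effect". No other term is named.
- **Adjustment.** The same section says that models with baseline covariates such as "severity of illness, admission status and variables with a large baseline imbalance will be fitted in secondary analyses". The list is open-ended and no threshold defines a large imbalance.
- **Secondary outcomes.** These analyses are exploratory: "Random effect linear models will be fitted to the continuous secondary outcome measures, analogous to the primary analysis".
- **Baseline data.** Baseline parameters lists "illness severity (CGI and GAF scores) and data on illness history", and for CANSAS-P says that "a 22-item questionnaire addressing patients’ needs for support in various domains will be applied". It also lists participation preference (API), PatPart-19, insight and perceived coercion at admission, and says that participation preferences may affect how patients perceive decision making.
- **Repeat measurements.** Under Secondary outcomes, unmet needs are assessed with the "Camberwell Assessment of Need self-report questionnaire (CANSAS-P) also at T1 and T2", and outpatient psychiatrists document "CGI and GAF scores at T2–T5". The text mentions no baseline SDM-Q-9; Table 1 is not shown.

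**The concern.** Three choices are involved.

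1. **Primary model.** Only 12 wards are randomised. Patients enter after their ward's condition is known to staff, and the Discussion itself names recruitment bias as a possible limitation. Some case-mix difference between arms is therefore plausible. The variables that could absorb part of it are collected but kept out of the primary model.
2. **Imbalance rule.** Whether a variable enters the adjusted model depends on the observed baseline data. A variable can be imbalanced and unrelated to SDM-Q-9, or nearly balanced and strongly related. The second kind is the more useful covariate, and the rule would leave it out. These adjusted models are the planned statistical check on case mix, so the check is partly left open.
3. **Own baseline.** SDM-Q-9 has no baseline in the text, so a model without one is natural there. Carried over by analogy to CANSAS-P, CGI and GAF, it drops what is usually the strongest predictor of a follow-up score.

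At stake are precision and partial protection against measured case-mix differences. The validity of the primary test is not at stake.

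**Working it through.** **Inputs from Sample size:** difference 15 points; within-cluster SD 30; ICC 0.04; 12 wards (6 per arm); 23 patients per ward; 20% dropout; two-sided 5%; 80% power. Evaluable patients per ward: 23 × 0.8 = 18.4.

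**Step 1: the plan's own figure.**
- Total variance = 900/0.96 = 937.5.
- Design effect = 1 + 17.4 × 0.04 = 1.696.
- Evaluable per arm = 2 × 937.5 × (1.960 + 0.842)²/15² × 1.696 = 110.9.
- Total after dropout = 2 × 110.9/0.8 = 277.3, against the stated 276.
- Power at 276 is 79.8% by the normal approximation. The sample size reproduces.

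**Step 2: unadjusted standard error.**
- Between-ward variance = 937.5 × 0.04 = 37.5.
- Variance of a ward mean = 37.5 + 900/18.4 = 37.5 + 48.9 = 86.4.
- SE = √(2 × 86.4/6) = √(86.4/3) = 5.37.
- With a noncentral t on 10 degrees of freedom (12 wards less 2 arms), power is 71%.

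**Step 3: effect of covariates.** The multiple correlation r with SDM-Q-9 is an assumption; the document gives none.
- Patient-level variance reduced only: SE = √((37.5 + 48.9(1 − r²))/3).
- Both levels reduced: SE = √(86.4(1 − r²)/3).

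| Assumed r | SE, patient level | Power, 10 df | SE, both levels | Power, 10 df |
|---|---|---|---|---|
| 0 | 5.37 | 71% | 5.37 | 71% |
| 0.1 | 5.35 | 71% | 5.34 | 72% |
| 0.3 | 5.23 | 73% | 5.12 | 75% |
| 0.5 | 4.97 | 78% | 4.65 | 83% |

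At r = 0.1 the gain is negligible. The right-hand columns also assume that patient covariates explain between-ward variance as well as within-ward variance.

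**Step 4: pair terms.** Table values hold without pair effects. Six pairs as fixed terms leave about 5 degrees of freedom for arm. With the same SEs, power on 5 df is 61% at r = 0; for r = 0.3 to 0.5 it is 63–68% (patient level) or 65–73% (both levels). Any reduction in between-ward variance from pairing is not credited here.

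**Step 5: size of chance imbalance.** For a covariate with an assumed ICC of 0.04 and no credit for matching, the standardised difference between arms has SD √(2 × 1.696/(6 × 18.4)) = 0.175, so a 95% range of about ±0.34. The resulting shift in the unadjusted estimate is correlation × 0.34 × 30: about 1 point at 0.1, 3 at 0.3 and 5 at 0.5. This is part of the variability already in the SE of 5.37, not an addition to it.

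**Step 6: own baseline.** Adjusting for the same scale's baseline leaves a fraction 1 − r² of the outcome variance. For an assumed r of 0.5 to 0.6 that is 0.75 to 0.64, so 25–36% is removed and the SE falls by 13–20%.

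**The case against.** The case for leaving the plan alone has real force.

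- **The primary model is a legitimate choice.** It is fixed in advance and, under ward randomisation, unbiased without inflated type I error. A reader might infer that the primary result is biased, or that its p-value can be steered by covariate selection. The text supports neither: covariates enter only secondary models, and the analysing statistician is blinded to allocation.
- **Adjustment is already planned.** Severity and admission status are named. What remains is which model is primary, plus the open part of the list. That stands, but the imbalance criterion is a rule the article states, not a detail left to an analysis plan.
- **Recruitment bias is addressed by design.** Recruitment is consecutive and monitored, refusals are documented, patients are not told of the randomisation or the intervention, and wards are matched. This stands. Measured covariates would reduce but not remove what is left.
- **The correlations are assumed.** This stands; at the low end there is almost no gain. A reader might also apply the table's powers to a model with arm, pair and covariates. Step 4 shows that they do not carry over.
- **Own-baseline terms concern exploratory outcomes.** This stands, and the analogy to the primary analysis does not forbid a baseline term. For CGI and GAF the rater and setting change between inpatient entry and outpatient follow-up, so their gain may be smaller than Step 6 suggests.

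**Conclusion.** The point holds as an improvement, not as a fault that invalidates the trial.

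- The primary model is valid, but it forgoes precision and partial protection against measured case-mix differences. Under the plan's own variance inputs and an assumed multiple correlation of 0.1 to 0.5, without pair terms, the loss ranges from almost nothing to 0.72 points of SE (5.37 to 4.65), or from under 1 to about 12 percentage points of power on 10 df.
- The imbalance rule is a poor criterion for choosing covariates. Its effect is confined to the secondary adjusted models.
- For CANSAS-P, CGI and GAF, no own-baseline term is stated where one is available. The 25–36% variance reduction rests on assumed correlations of 0.5 to 0.6 and is least secure for CGI and GAF.

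The stated sample size is not in question on this point.

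**What to change.** 1. **Primary model:** keep ward as random effect and arm as fixed effect, and add a short pre-specified list of baseline covariates, for example CGI, admission status, diagnosis (F20 or F25) and number of previous hospitalisations. Report the unadjusted model as sensitivity analysis.
2. **Adjusted secondary models:** replace the imbalance criterion with a list chosen in advance on expected prognostic value. API and insight are candidates, given the protocol's own reasons for collecting them.
3. **CANSAS-P, CGI and GAF:** state that each model includes the baseline value of the same scale.
4. **Pairs:** decide separately whether to include pair. Fixed pair terms cut the degrees of freedom from 10 to about 5, so the decision should not ride on the covariate change.

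The cost is analysis wording; nearly all the data are already planned for collection. Missing baseline values need simple imputation so that patients with an outcome are not lost. Recruitment bias from unmeasured differences remains and should still be reported as a limitation.

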### Aim and hypotheses

The aim of the present study is to evaluate the effects of SDM-PLUS on decision making patterns on acute psychiatric wards between psychiatrists and patients suffering from schizophrenia. We hypothesize that the intervention will lead to professionals and patients using the skills learned in the SDM-PLUS training for professionals or the SDM-training for patients, respectively, leading to a higher perceived involvement of patients. We argue that a better (perceived) involvement of patients in medical decisions would be a benefit per se [2]. However, a higher perceived involvement from the patients’ side may also have an effect on the therapeutic alliance finally resulting in better adherence and fewer relapses caused by non-adherence [21, 22] (Fig. 1).

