### Participants

The study will be implemented in 12 acute psychiatric wards (=clusters) of 5 psychiatric state hospitals. Eligibility criteria for the wards to be included are: acute psychiatric ward in one of the participating hospitals, patients with schizophrenia or schizoaffective disease are commonly treated on these wards. The respective wards have 300–600 admissions per year of which approximately 20–50% of patients meet inclusion criteria.

All patients fulfilling the inclusion criteria will then be consecutively recruited for the trial at the time of their admission to the ward.

Inclusion criteria:age 18–65 yearsmale and female patientsinpatients of participating hospitalsdiagnosis of schizophrenia or schizoaffective disease (ICD 10: F20/F25)capable of participating in 60 min. group interventionbeing able to provide written informed consent

Exclusion criteria:mental retardationinsufficient proficiency in German language to discuss treatment decisions

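### The Baron and Kenny criteria make mediation depend on a significant total effect that this trial is poorly placed to detect, and give no interval for the indirect effect (minor, exploratory)

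*Protocol article*

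**What the plan says.** The Statistical analyses section places mediation among the secondary-outcome work, introduced by "Exploratory analyses will be performed to assess the effect of the intervention on the secondary outcome measures". It then states that "it will be assessed if SDM is a mediator for the secondary outcomes following the criteria of Baron and Kenny". No indirect-effect estimate, test or interval is named. The sentences that follow give the outcome models: "Random effect linear models will be fitted to the continuous secondary outcome measures, analogous to the primary analysis", where the primary analysis has ward as a random effect, and "For binary secondary outcome measures, logistic regression models using GEEs will be fitted".

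The chain to be examined is set out under Aim and hypotheses: higher perceived involvement "may also have an effect on the therapeutic alliance finally resulting in better adherence and fewer relapses". Treatment is assigned by ward ("randomize one ward of each pair to the intervention and one ward to the control condition"), with 12 wards in all. SDM-Q-9 is completed by each patient.

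On timing, the Secondary outcomes section says of the downstream outcomes: "These outcomes will be obtained at T1 (three weeks after study enrolment", and then quarterly over a year (T2–T5). In detail, treatment satisfaction (ZUF8) and the difficult-decisions interview are at T1, and unmet needs (CANSAS-P) are at T1 and T2. Alliance (HAS), adherence (MARS) and documented rehospitalisation are at T2–T5.

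**The concern.** The criteria are a chain of significance tests: group on outcome, group on mediator, then mediator on outcome given group. The first link is the weak one here. If involvement is the route to better adherence, the group effect on adherence is the product of two paths and so is smaller than the effect on SDM-Q-9 for which the trial was sized. The chain can then stop at its first step even when both component paths are detectable.

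A report of no mediation on that basis could be read as evidence against the model that motivates the trial, when it reflects little more than low power for the total effect. Readers would also have no indirect effect with an interval to show what the data do and do not exclude. This concerns a method that the article names, not a detail it leaves to another document.

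**Working it through.** **Inputs from the article.** Difference 15, within-ward SD 30, ICC 0.04, two-sided 5%, 80% power, 20% dropout, 12 wards of 23 (Sample size). Evaluable patients per ward: 23 × 0.8 = 18.4.

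**Inputs assumed, because the article gives none.** Standardised slope of outcome on SDM-Q-9, b = 0.2, 0.3 or 0.5; ICC 0.04 for the secondary outcomes as well; complete mediation unless a direct effect is stated; continuous outcomes.

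**1. The planned sample size.**
- Total SD = 30/√0.96 = 30.62.
- n per arm before clustering = 2 × [30.62 × (1.960 + 0.842)/15]² = 65.4.
- Design effect = 1 + (18.4 − 1) × 0.04 = 1.696.
- Evaluable total = 2 × 65.4 × 1.696 ≈ 221.9; enrolled = 221.9/0.8 ≈ 277, against 276 stated. The figure is reproduced.

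**2. Size of the passed-on effect.** Total effect = a × b + direct effect. With a = 15/30 = 0.5 and no direct effect, b = 0.2, 0.3, 0.5 gives 0.10, 0.15, 0.25 SD.

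**3. Power for the total effect.** In SD units, SE = √[2 × (0.04 + 0.96/18.4)/6] = 0.175. Power follows from effect/SE, by normal reference and by t with 12 − 2 = 10 df.

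| Total effect (SD) | Normal | t, 10 df |
|---|---|---|
| 0.10 | 8% | 8% |
| 0.15 | 14% | 12% |
| 0.25 | 30% | 25% |
| 0.30 | 40% | 34% |
| 0.40 | 63% | 54% |
| 0.50 | 81% | 73% |

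Over ICC 0.01 to 0.10 (t, 10 df), power runs from 15% down to 9% at 0.15 SD and from 46% down to 23% at 0.30 SD. With half the patients lost by follow-up (assumed; 11.5 per ward, ICC 0.04), it is 10% at 0.15 SD and 27% at 0.30 SD.

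**4. Success of the two procedures.** Simulation of 12 wards × 18 patients, a = 0.5 SD, at least 4,000 trials per scenario. The a path and the total effect are tested on ward means (t, 10 df) and the b path on within-ward deviations. The within-ward and between-ward slopes are equal by construction.

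| b | Direct effect (SD) | Total effect (SD) | Baron and Kenny steps | Joint test of a and b |
|---|---|---|---|---|
| 0.2 | 0 | 0.10 | about 5% | about 60% |
| 0.3 | 0 | 0.15 | about 10–11% | about 71% |
| 0.5 | 0 | 0.25 | about 21–23% | about 73% |
| 0.3 | 0.15 | 0.30 | about 26–27% | about 71% |
| 0.3 | 0.35 | 0.50 | about 54–55% | about 72% |

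The joint test is capped by the a path, whose own power is about 73%. The first column of results is lower because the total effect must be significant too.

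**5. What if the slopes are not assumed equal?** A treatment given to whole wards can act only through the ward-level part of the mediator. A model that splits the mediator into ward mean and within-ward deviation therefore takes its indirect effect from the slope across 12 ward means (9 df). A joint test of a and that between-ward slope succeeds in about 7%, 10% and 25% of trials for b = 0.2, 0.3 and 0.5, close to the Baron and Kenny steps.

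**The case against.** The strongest reply is that low power comes mainly from having 12 wards, and that the gain from removing the total-effect step is bought with an assumption. Step 5 of the working bears this out: without equal within-ward and between-ward slopes, most of the gain goes. This stands. It is why the split model cannot be the main analysis and why the assumption has to be stated.

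Second, a reader might infer that a trial of this size almost cannot show a total effect on a secondary outcome. The article does not support that. It gives no secondary effect size and no slope, and power is 73–81% at 0.5 SD and 54–63% at 0.4 SD. Complete mediation is also not the article's own model: the Secondary outcomes section credits better handling of difficult decisions as well as involvement, and the Discussion names extra attention as a possible driver of change in perceived involvement. A direct effect narrows the gap between the procedures but does not close it.

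Third, a reader might infer that ward-level treatment with a patient-level mediator rules out a valid indirect effect. It does not. The planned ward random-effects models accommodate that structure and, for continuous outcomes, give the path coefficients. What is missing is the combination of those coefficients into an indirect effect with an interval.

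Fourth, a reader might infer that the outcomes are concurrent with the mediator and so uninformative on direction. That holds for ZUF8, the difficult-decisions scores and the T1 CANSAS-P only. Alliance, adherence and rehospitalisation already follow T1.

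Finally, the choice of mediator time point, covariates and centring may be settled in a fuller document that is not shown. Their absence is not counted against the article. They appear under the fix only because the replacement analysis needs them.

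**Conclusion.** The point holds as a minor one. The article fixes a mediation procedure whose classical form stops at a non-significant total effect and yields no interval for the indirect effect. For passed-on effects of about 0.10–0.25 SD, total-effect power is about 8–30%. Under complete mediation the criteria would succeed in about 5–23% of trials, against about 60–73% for a joint test. With a direct effect raising the total to 0.3–0.5 SD, the contrast is about 27–55% against 71–72%.

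These figures rest on a = 0.5 SD as planned, assumed slopes of 0.2–0.5, ICC 0.04 for the outcomes, about 18 evaluable patients per ward, continuous outcomes, and equal within-ward and between-ward slopes. The joint-test advantage depends on the last of these. The analysis is exploratory, and the primary comparison of SDM-Q-9 is untouched.

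**What to change.** Replace the reference to the Baron and Kenny criteria with the following.

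- Do not require a significant total effect.
- Take SDM-Q-9 at T1 as the mediator and outcomes measured at T2–T5. Leave outcomes measured only at T1 out of the mediation analysis.
- Fit the mediator and outcome models with the ward random effect already planned, adjusted for baseline insight (Birchwood Insight Scale), API and CGI, all of which are collected.
- Report the indirect effect with a 95% confidence interval, by Monte Carlo or a ward-level bootstrap, and describe it as exploratory.
- As a sensitivity analysis only, report the model that splits the mediator into ward mean and within-ward deviation, with a note on its low power with 12 wards.
- State that the main estimate assumes equal within-ward and between-ward slopes and no unmeasured confounding of mediator and outcome.

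The cost is modest analyst time, with no new data. The drawback is that the main estimate leans on those two assumptions, and the sensitivity analysis will be too imprecise to check the first of them well.
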